### Sampling methods

A proportionate random sampling was applied. The HIV databases from each clinic were obtained from the Selangor State Health Department to look for the list and the total number of patients in each clinic. Then, the required number of MSM in each clinic was calculated based on proportion to get 941 MSM. To build trust with the MSM and ease the data collection process, the researchers engaged with HIV clinic nurses and appointed them as research nurses. Next, the lists of MSM in each clinic were obtained to screen them for inclusion and exclusion criteria. Based on the screened name list of MSM in each clinic, random sampling is conducted to select the required number of MSM using a randomizer application. New master lists of selected MSM were extracted in an Excel sheet that contained their personal information, clinical information, and the clinic appointment date to remind the researcher to ask for written consent and to collect the data when the MSM visit the clinic. From the list, the researcher will create and insert a code to replace the MSM’s names on the questionnaire and during the in-depth interview.

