### Specific objectives for quantitative study

To determine the prevalence of depressive symptoms among the MSM living with HIV in Selangor.To describe the distribution of biological, psychological, and social factors of depressive symptoms among MSM living with HIV in Selangor.To determine the association between biological, psychosocial, and social factors and depressive symptoms among MSM living with HIV in Selangor.

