### Settings

Both study phases will be conducted in ten Primary Care Clinics in Selangor with the highest number of MSM living with HIV registered. Selangor has been chosen as the study location as a previous study shows a high prevalence of depressive symptoms among MSM in Selangor (10). Quantitative data collection was conducted from March 2022 to February 2023, while qualitative data collection is from March 2023 to April 2023.

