#### Data analysis for quantitative study

Data will be collected and analyzed using the IBM Statistical Package for Social Science (SPSS) version 25, involving descriptive and inferential statistics. The descriptive statistics will describe the MSM’s characteristics: mean, standard deviation, mode, median, interquartile range, and percentage. Cross-tabulation and frequency counts will be used to assess the demographic items and the MSM’s responses to survey scales. The data analysis utilizes both univariate and multivariate statistical methods. Simple logistic regression will be used to measure the associations between independent and dependent variables. A less rigorous threshold, such as a P-value < 0.25, should be applied to prevent omitting crucial variables from a model due to stochastic variation [38, 39]. Therefore, variables with a P value < 0.25 will be included in multiple logistic regression to measure the predictors of depressive symptoms. The binary outcomes of depressive symptoms will use a cut-off score ≥10. The scores of 0 to 9 represent none to subthreshold depression, and a score of 10 and above represents a patient’s spectrum to possible major depression [40]. The level of significance at 0.05 and 95% confidence interval (CI) will be used to yield a significant result.

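### Clinic quotas were set before eligibility screening on a loosely stated size measure, and the described analysis provides for neither clinic nor weights

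*Protocol article*

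**What the plan says.** Under Settings, the study takes place in "ten Primary Care Clinics in Selangor with the highest number of MSM living with HIV registered".

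Under Sampling methods, the steps run in this order:

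1. The scheme is named: "A proportionate random sampling was applied".
2. HIV databases were obtained from the state health department "to look for the list and the total number of patients in each clinic".
3. Quotas were set: "Then, the required number of MSM in each clinic was calculated based on proportion to get 941 MSM".
4. Eligibility was checked: "Next, the lists of MSM in each clinic were obtained to screen them for inclusion and exclusion criteria".
5. Selection followed: "Based on the screened name list of MSM in each clinic, random sampling is conducted to select the required number of MSM".

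For the analysis, the section on the quantitative study says "Simple logistic regression will be used to measure the associations between independent and dependent variables". Variables with a P value below 0.25 then enter a multiple logistic regression. The questionnaire variables under Study instruments do not include clinic, and neither section mentions strata or sampling weights.

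The first quantitative objective is "To determine the prevalence of depressive symptoms among the MSM living with HIV in Selangor". The general objective and the other specific objectives also refer to Selangor.

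**The concern.** A proportionate stratified sample is self-weighting when the size measure behind the quotas is proportional to the population being sampled. Here that population is eligible MSM. The quotas, however, rest on a count taken before screening, and that count is described only as patients. If the eligible fraction of the count differs between clinics, so does an eligible man's chance of selection. Unequal response would add to this.

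Two results could be affected. The pooled prevalence would give some clinics more or less than their share of eligible MSM. In the regression, clinic may stand for differences in catchment and care. It is not a listed candidate variable, so the P < 0.25 rule would not bring it in.

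Separately, the clinics were chosen for their size rather than sampled, so the estimates describe MSM registered at those clinics. The objectives claim more than that.

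**Working it through.** **The stated total.** The quotas share out 941. With proportions 0.55 and 0.45, two-sided 0.05, 80% power and pooled variance, n = (1.96·√0.5 + 0.8416·√0.495)² / 0.10² = 391.3, so 392 per group. Then 392 × 2 = 784, and 784 × 1.2 = 940.8, so 941. This reproduces the article's total. (The coefficient 0.62 printed in the formula would give about 330 per group; that is a separate matter.) The point here contests how 941 is divided and analysed, not the figure itself.

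**When the unweighted prevalence is off.** In clinic c, let T be the count used for the quota, e the eligible share of T, r the response rate and p the prevalence.

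- Respondents are proportional to T·r, and eligible MSM to T·e.
- The correct weight is therefore proportional to e/r.
- With equal response, unweighted minus weighted prevalence = −cov(e, p) / mean(e), taken over clinics with T as weight.

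This is zero if e is constant, if p is constant, or if the two are unrelated across the clinics.

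**One worked case (assumed inputs).** Take ten clinics with equal T, e equally spaced from 0.40 to 0.80, and p from 0.30 to 0.55, rising together.

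- cov = 8.25 × (0.40/9) × (0.25/9) = 0.0102, and mean(e) = 0.60.
- Shift = 0.0102/0.60 = 1.7 points: 42.5% unweighted against 44.2% weighted.
- With p from 0.35 to 0.50, cov = 0.0061 and the shift is 1.0 point: 42.5% against 43.5%.

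**A range of cases (assumed inputs).** T is drawn uniformly from 100 to 400, mean prevalence is 45%, and e is drawn uniformly over the range shown. In the third and fourth columns prevalence is unrelated to e. In the fifth it moves in perfect step with e. Shifts are in percentage points.

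| Eligible share | Between-clinic SD of prevalence | Mean absolute shift | 95th percentile | Perfect step (mean size) | Kish factor |
|---|---|---|---|---|---|
| equal | 5 or 10 | 0 | 0 | 0 | 1.00 |
| 40–60% | 5 | 0.14 | 0.36 | 0.53 | 1.01 |
| 40–60% | 10 | 0.28 | 0.72 | 1.07 | 1.01 |
| 30–70% | 5 | 0.28 | 0.73 | 1.07 | 1.05 |
| 30–70% | 10 | 0.57 | 1.44 | 2.14 | 1.05 |
| 20–80% | 5 | 0.43 | 1.12 | 1.62 | 1.11 |
| 20–80% | 10 | 0.86 | 2.20 | 3.25 | 1.11 |

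**Yardstick.** If 20% of 941 do not respond, 0.8 × 941 = 753 remain. The half-width at 50% prevalence is 1.96 × √(0.25/753) = 3.6 points. It would be 3.5 at 784 and 3.2 at 941.

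**Precision lost by weighting.** At the largest Kish factor, the half-width grows by √1.11 = 1.05, from 3.6 to about 3.8 points.

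**Odds ratios.** No calculation is possible. Unequal sampling fractions alone do not bias them. Clinic would have to be associated with the predictor and with depressive symptoms after the other covariates, and the article gives no information on either association.

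**The case against.** The case against has four parts.

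**The quota base is not stated.** A reader might infer that quotas were proportional to all HIV patients. The article does not say so. The clinics were picked by number of registered MSM, and MSM status comes from the clinic database, so MSM counts were available. If they were used, only nationality, language, age and known psychiatric disorder separate the base from eligible MSM, and shares would probably vary much less than in the wider ranges above. This stands. What remains is that the base is unclear and no step after screening corrects it.

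**Silence is not a decision.** A reader might infer that the investigators chose to ignore clinic. A condensed article may leave strata and weights to a fuller document, so that inference fails. The article does, however, fix a rule for entry into the model and list the variables collected. Clinic is not among them, and a design stratum should not depend on a P-value screen in any case.

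**Odds ratios may already be protected.** Ethnicity, income, residence, education, employment, CD4 level and viral load are collected and are candidates for the model. They may absorb much of what clinic would carry. This stands, and it is why no claim of biased odds ratios can be made.

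**The worked case is unfavourable by design.** It has eligible share doubling across clinics with prevalence in perfect step. Nothing in the article suggests that pattern, and the shift is still under half the half-width.

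A further tempting reading is a cluster design effect: at an assumed intraclass correlation of 0.01, 1 + (94.1 − 1) × 0.01 = 1.93 for 941 patients. It does not apply to inference about these ten clinics, because all ten are sampled as strata.

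**Conclusion.** The point holds in a limited form. The documented order of steps and the vague size measure do not guarantee equal selection probability among eligible MSM, and the described analysis makes no use of the strata.

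For prevalence, the bias depends on eligible share or response differing by clinic and being related to clinic prevalence. It is zero if shares and response are equal, typically under 1 point, and about 2 to 3 points in extreme assumed cases, against a half-width of about 3.6 points. All of these sizes rest on assumed clinic sizes, shares and prevalences, because the article gives none. For odds ratios, confounding by clinic is possible but neither shown nor measurable here.

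The mismatch between the ten highest-volume clinics and objectives worded for Selangor needs no assumption. It is a matter of target population, and weighting would not cure it.

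This is a worthwhile improvement at low cost. It does not show that the planned results would be wrong.

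**What to change.** Quantitative data collection is reported as running to February 2023, so resetting the quotas would come too late. The remedy lies in the analysis and the wording:

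- State which count the clinic quotas were proportional to, and report for each clinic the eligible MSM on the screened list, the number selected and the number responding.
- Include clinic (10 levels) in the multiple logistic model regardless of the P < 0.25 screen.
- Report prevalence as a stratified estimate, with weight = eligible MSM on the clinic's screened list / respondents in that clinic. This corrects for non-response only if response is ignorable within clinic, and the report should say so.
- Word the target population as eligible MSM registered at these ten highest-volume clinics, rather than all MSM living with HIV in Selangor.

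Cost: 9 degrees of freedom in the model, and intervals for prevalence up to about 5% wider under the ranges assumed above. No new data should be needed, since the eligible counts come from the screened lists already drawn up.

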### Study instruments

A self-administered paper-based questionnaire will be used for this study to reduce non-response rates, as seen in another study [28]. A comprehensive translation will be done in Malay and English by those proficient in both languages. It will be distributed to the MSM in Malay or English based on their preference. The questionnaire will be divided into six sections, as follows:

Section 1 for sociodemographic factors and clinical information
Age, ethnicity, religion, residence, education level, marital status, employment status, monthly personal income, family history of psychiatric disorders, smoking status, CD4 level, viral load level, and other chronic diseases.Section 2 for depressive symptoms score
Patient Health Questionnaire-9 (PHQ-9) was used to assess the severity of depressive symptoms, which includes nine items that focus on the Diagnostic and Statistical Manual of Mental Disorders, 4th edition (DSM-IV) for Major depressive disorder. The questionnaire measures the frequency with which each of the nine things bothered the individuals during the immediately preceding two weeks. Each item of PHQ-9 was scored on a scale of 0–3 (0 = not at all; 1 = several days; 2 = more than a week; 3 = nearly every day). The PHQ-9 total score ranges from 0 to 27 (scores of 0–4 as none; 5–9 as mild depression; 10–14 as moderate depression; 15–19 as moderately severe depression; and ≥ 20 as severe depression) [29].Section 3 for HIV-related stigma
The 12-item short version of the HIV stigma scale was used to assess HIV-related stigma. The questions were further divided into four domains; personalized stigma, disclosure, negative self-image, and public attitudes. Responses were totaled to produce subscales ranging from 3 to 12 points; higher scores reflect a higher level of perceived HIV-related stigma [30].Section 4 for social support
The Scale of Perceived Social Support in HIV (PSS-HIV) was selected. The scale can give valuable data to establish strategies related to each person-specific level of needs and context and, thus, integrate into a practical tactic, a systemic hands-on approach for people living with HIV (PLHIV). The scale resembles the three top levels of Maslow’s hierarchy of needs, composed of three sub-scales: (a) Belonging: the basic needs of support and safety; (b) Esteem: the acceptance, affection, and help from others; and (c) Self-development: the perception of achieving individual growth. The scale used 12 Likert-type items; all scored 1–5, with possible overall scores ranging from 12 to 60. Higher scores will indicate a higher Perceived Social Support [31].Section 4 for high-risk behavior
The study will use the HIV sexual risk scale with nine items [32]. The questions will assess the history of high-risk sexual behavior in the past three months. All questions require the participant to answer “Yes” or “No.”. If they answer ‘yes’ to any of the questions, they will be categorized as ‘had recent high-risk behavior.’Section 5 for risk for sexualized substance use
Substance use questions will adopt the sociodemographic items from a study among MSM in Singapore by Tan et al. (2021) [33]. The questions will assess the history of sexualized alcohol use, sexualized drug use (amyl nitrite, methamphetamine, and Gamma-hydroxybutyrate/Gamma-butyrolactone), and ever-use erectile dysfunction drugs for sex. All questions require the participant to answer “Yes” or “No.”

### Study processes

#### a) Quantitative data collection

The researcher or research nurses will approach the MSM to participate in the study during clinic appointments or clinic visits. The research team had opportunities to recruit the MSM on different dates during doctor’s follow-ups, pharmacist appointments, and blood-taking appointments. Research nurses are crucial in assisting research teams, ensuring that studies run efficiently and that MSM are safe and well-informed. They are eligible to recruit, gain consent, and collect data from the MSM. The researcher will explain the study protocol and obtain written consent from the MSM after a clinic visit in the consultation room or any available room in the clinic. Subsequently, the eligible MSM will be given a self-administered questionnaire to obtain the required information. After the MSM answer the questionnaire, their PHQ-9 score will be obtained on the spot. For ethical reasons, participants with moderate to severe depressive symptoms will be referred to Medical Officer at the respective clinic for further assessment.

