Depression among MSM has significant effects on public health. Depression affects physical, educational, social, economic, psychological, and short- and long-term health effects for MSM living with HIV [12]. The presence of depressive symptoms may reduce an individual’s motivation to engage in self-care and thus increase the likelihood of risky behavior and suicide [13, 14]. Among MSM living with HIV that have compulsive sexual behavior, having sex can become an alternative strategy to cope with negative emotions such as loneliness, anxiety, and stress [15]. Regarding viral load suppression, depression is a risk factor for ‘imperfect’ antiretroviral therapy (ART) adherence among MSM living with HIV that could jeopardize the Treatment as Prevention (TasP) strategy [16]. More importantly, the co-occurrence of HIV and depression was related to adverse health outcomes, such as low quality of life and deterioration of disease conditions [17].

A complicated combination of biological, psychological, and social variables could cause depression [3]. Therefore, the biopsychosocial approach has been used to structure guidelines, is used clinically, and discusses person-centered care, which can improve patient outcomes [18, 19]. The factors that increase depression among MSM living with HIV include younger age, unemployment, smoking, externalized HIV stigma, not being on ART, lack of self-efficacy, and low social support [20]. In addition, MSM are prone to mental health problems owing to sexual minority stress, homophobia, persecution based on sexual orientation, and stigmas that prevent healthy behavior [21, 22].

Addressing the mental health concerns of individuals living with HIV is essential to providing quality HIV care [9]. In many low and middle-income countries, MSM have fewer resources and are more likely to be hidden and stigmatized, compounding HIV acquisition and transmission risks and limiting access to the most basic services [23]. Continuing research, additional resources, political will, policy change, institutional transformation, community participation, and strategic planning and programming will be required to combat the increasing prevalence of depression among MSM living with HIV.

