This study applies integration at all study stages, where it occurs during study design, methods level, and interpretation and reporting levels. Regarding study design, the researcher gathers and analyzes quantitative data first, then uses those results to guide the collection and analysis of qualitative data. Meanwhile, integration at the methods level occurs through connecting, building, and merging approaches. The connecting approach occurs when the interview MSM are selected from those who responded in the quantitative phase. Integration through building occurs when the results from the quantitative phase inform the data collection approach for the qualitative phase, where the selected MSM will be those with PHQ-9 scores ≥ 10. Integration through data merging occurred in this study when parallel questions with the quantitative phase were used in the qualitative phase. The researchers also will merge the PHQ-9 scores and MSM interview data to understand better how qualitative results explain quantitative results. Finally, integration at the interpretation and reporting level occurs when the researchers combine the data through a joint display table. The table will have three columns: (1) Quantitative results; (2) Qualitative interview explaining quantitative results; and (3) How qualitative findings help to explain quantitative results.

Pragmatism is a choice paradigm in this sequential explanatory sequential mixed methods study. It combines objective and subjective evidence that makes this design suitable for explaining complicated issues in public health, such as depressive symptoms among the MSM population. Fig 1 shows the Conceptual framework of explanatory sequential mixed methods study design on predictors of depressive symptoms among MSM living with HIV. Phase 1 will be the quantitative data collection, followed by the interface point. The MSM with moderate to severe depressive symptoms will be identified. The study then enters phase two, where qualitative data collection using an in-depth interview will be carried out among the MSM with moderate to severe depressive symptoms.

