#### Study sampling and procedure for qualitative phase

Purposive sampling will be chosen in the qualitative phase. The MSM will be chosen from those with moderate to severe depressive symptoms or those with a PHQ-9 score of ≥ 10 from the quantitative study. Sample size guidelines suggested an adequate range between 20 and 30 interviews [35]. Therefore, 20 MSM will be selected for the qualitative study. Suppose all or most MSM in the quantitative phase have moderate to severe depressive symptoms. Those with severe depressive symptoms will be chosen first, followed by moderately severe depressive symptoms and moderate depressive symptoms. The justification for this method is that the quantitative and qualitative data and their analysis might clarify and explain the statistical results through a more in-depth examination of the MSM’s perspectives.

The study sampling is relatively small compared to the quantitative method, as it depends on the saturation point where no new information is acquired from the following interview. Data saturation is achieved when: (1) there is adequate information to replicate the study; (2) when the capacity to acquire new information has been attained; and (3) when further coding is no longer feasible [36].

Only the main researcher will conduct the in-depth interview for the qualitative study. The researcher will approach the selected MSM at the clinic during clinic visits. The researcher will explain the study protocol and obtain written consent from the participants after a clinic appointment in the consultation room or any available room in the clinic. The room used for the interview will be identified prior to the interview with permission from the clinic’s head. Subsequently, an in-depth interview will be conducted to obtain the information required and will be voice recorded using two voice recorder devices. The interview will require MSM to tell their experiences regarding their depressive symptoms according to the biopsychosocial approach.

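### The only printed referral rule is set on overall PHQ-9 severity, so endorsing the suicidality item with a total of 9 or less leads to no stated referral

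*Protocol article*

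**What the plan says.** Under Study processes, a) Quantitative data collection, the protocol article says that after the participant completes the questionnaire "their PHQ-9 score will be obtained on the spot", and that for ethical reasons "participants with moderate to severe depressive symptoms will be referred to Medical Officer at the respective clinic for further assessment". That sentence gives no numerical cut-off. The level is fixed elsewhere:

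- **Study instruments** gives the bands, including "5–9 as mild depression; 10–14 as moderate depression". Totals of 0 to 4 are labelled none. Each of the nine items is scored 0 to 3.
- **Study design** selects interviewees by the same threshold: "where the selected MSM will be those with PHQ-9 scores ≥ 10".
- **Study sampling and procedure for qualitative phase** pairs the severity wording with the number: "moderate to severe depressive symptoms or those with a PHQ-9 score of ≥ 10 from the quantitative study".
- **Data analysis for quantitative study** uses it for the outcome: "The binary outcomes of depressive symptoms will use a cut-off score ≥10".

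On content, Study instruments describes the PHQ-9 as an instrument "which includes nine items that focus on the Diagnostic and Statistical Manual of Mental Disorders, 4th edition (DSM-IV) for Major depressive disorder". The Introduction lists suicidality among the symptoms of depression and says that depressive symptoms may weaken self-care and "thus increase the likelihood of risky behavior and suicide".

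The two confidentiality sections under Safety considerations cover data protection, and the closing section on suspension covers stopping the study. Neither adds a referral rule.

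**The concern.** A total score and a single answer carry different information. The total measures overall symptom burden. A positive answer about suicidality may call for attention even when the other items are low. A rule keyed only to the total attaches no action to that answer until enough points accumulate elsewhere.

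What is at stake is participant safety. The form is scored while the participant is still at the clinic and a route to a Medical Officer already exists, so the answer is available when it could be acted on. Participants below 10 are also not selected for interview, so the second phase gives no later occasion on which the answer would be explored. The prevalence estimate, the regression models, power and the significance level are all unaffected.

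**Working it through.** **Inputs**

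- Nine items, each scored 0 to 3, total 0 to 27 (Study instruments).
- Bands: 0–4 none, 5–9 mild, 10–14 moderate, with two higher bands above (Study instruments).
- Referral at moderate or above (Quantitative data collection), taken as a total of at least 10 (Study design, Study instruments, Study sampling and procedure for qualitative phase, and Data analysis for quantitative study, which all agree).
- Inferred, not printed: one of the nine items asks about suicidality. The Introduction lists eight symptoms, suicidality among them, and names depressed mood separately. Together these make nine, which matches the number of items.

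**Is the threshold consistent?** Yes. All four sections put the line at 10, so the plan does not contradict itself. There is no sample-size or power figure to reproduce for this point.

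**Which answers stay below the line?** Let s be the suicidality answer (1, 2 or 3) and r the sum of the other eight items. No referral is stated when s + r ≤ 9, that is, when r ≤ 9 − s.

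| s | r with no stated referral | Total | Labelled none (total ≤ 4) | Labelled mild (total 5–9) |
|---|---|---|---|---|
| 1 | 0–8 | 1–9 | r = 0–3 | r = 4–8 |
| 2 | 0–7 | 2–9 | r = 0–2 | r = 3–7 |
| 3 | 0–6 | 3–9 | r = 0–1 | r = 2–6 |

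At the top answer of 3, referral is stated only once the other eight items contribute 7 or more (3 + 7 = 10). With 0 or 1 point elsewhere, the total is 3 or 4 and the plan's own label is none.

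**Is the gap closed elsewhere?** The article contains no single-item trigger, no suicide-risk procedure and no referral for totals of 9 or less.

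**What cannot be computed.** Of the 3 × 4⁸ = 196,608 possible response patterns with a non-zero suicidality answer, 8,938 + 5,115 + 2,643 = 16,696 have a total of 9 or less (for s = 1, 2 and 3 in turn). This shows only that the situation is possible at every answer level. Patterns are not equally likely, so the count is not a prevalence. The article gives no item-level rates, and no number of participants can be derived.

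**The case against.** The strongest reply is that this is a condensed article. A distress or suicide-risk procedure would commonly sit in the full protocol or the ethics submission, and ethics approval is cited. The referral sentence does not say that only those participants are referred. Participants are patients of the clinics where they are recruited, the research nurses are those clinics' own HIV nurses, and part of their stated role is to keep participants safe. The standard that any positive answer should prompt referral is not itself in the document, and the Introduction's link to suicide concerns depressive symptoms in general, not one item at a low total. Finally, Settings reports that quantitative collection ran from March 2022 to February 2023, and no further use of the PHQ-9 is described.

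Much of this stands, and it limits what may be concluded. A reader might infer that staff are forbidden to refer below 10, that the study has no suicide-risk safeguard, or that at-risk participants were in fact missed. The document supports none of these: referral is not restricted, unseen documents may hold a fuller procedure, and the frequency is unknown.

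What does not stand is that the point is merely missing detail. The article prints a concrete referral rule with a stated trigger, and that trigger is overall severity. Clinic contact and nurse involvement are real safeguards, but they attach no stated action to this answer. Consent is obtained after a clinic visit and the questionnaire follows, and some approaches take place at pharmacist or blood-taking appointments, so a doctor's consultation need not come afterwards.

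**Conclusion.** The point holds as a narrow one: the printed rule is keyed to overall severity, and below a total of 10 no referral is stated for a participant who endorses the suicidality item at any level, including the highest.

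It rests on two assumptions. One is that moderate to severe in the referral sentence means a total of 10 or more, which four other sections support consistently. The other is that one PHQ-9 item covers suicidality, which is a reasonable inference but not printed.

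In size, the gap covers totals of 1 to 9 with a non-zero answer on that item, in an unknown number of participants. It is a lower-priority safety improvement: cheap and worthwhile, but with limited practical reach because collection is reported as complete.

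**What to change.** Add one sentence to the referral rule under Quantitative data collection: any non-zero answer on the suicidality item also triggers same-visit referral to the clinic's Medical Officer, whatever the total. State the cut-off of 10 in the same place so that the rule can be read without other sections. If a fuller procedure already exists in the full protocol or ethics file, refer to it and align this sentence with it.

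The change uses the existing on-the-spot scoring and the existing Medical Officer route. Its cost is an unknown number of additional referrals. It applies to any remaining or future use of the questionnaire and does not reach those already surveyed.

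Whether stored forms with totals below 10 warrant review and re-contact is a separate question for the ethics committee and not part of this cheap fix. The answers describe a two-week period that may be months past, and re-contact would mean re-linking identities through a restricted code list in a group facing legal and social difficulties.
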